## Abstract

Once-daily (od), low-dose aspirin (75–100 mg) is recommended to reduce the thrombotic risk of patients with essential thrombocytemia (ET). This practice is based on data extrapolated from other high-risk patients and an aspirin trial in polycythemia vera, with the assumption of similar aspirin pharmacodynamics in the two settings. However, the pharmacodynamics of low-dose aspirin is impaired in ET, reflecting accelerated renewal of platelet cyclooxygenase (COX)-1. ARES is a parallel-arm, placebo-controlled, randomized, dose-finding, phase II trial enrolling 300 ET patients to address two main questions. First, whether twice or three times 100 mg aspirin daily dosing is superior to the standard od regimen in inhibiting platelet thromboxane (TX)A_2_ production, without inhibiting vascular prostacyclin biosynthesis. Second, whether long-term persistence of superior biochemical efficacy can be safely maintained with multiple vs. single dosing aspirin regimen. Considering that the primary study end point is serum TXB_2_, a surrogate biomarker of clinical efficacy, a preliminary exercise of reproducibility and validation of this biomarker across all the 11 participating centers was implemented. The results of this preliminary phase demonstrate the importance of controlling reproducibility of biomarkers in multicenter trials and the feasibility of using serum TXB_2_ as a reliable end point for dose-finding studies of novel aspirin regimens.

## Introduction and rationale

Essential thrombocythemia (ET) is a myeloproliferative neoplasm (MPN) characterized by clonal thrombocytosis and enhanced risk of arterial and venous thrombosis^1–3^. The discovery of the *JAK2 V617F* mutation in 2005 and the revised 2008 World Health Organization (WHO) guidelines^4^ indicating a lower platelet count threshold for diagnosing ET, led to an apparent increase in ET incidence^5^. Nowadays, ET incidence approximates 1.0–1.7 per 100 000 individuals per year, with a likely increase in the near future due to the continuous rise of occasional, asymptomatic diagnoses, and an estimated prevalence of approximately 20 per 100 000 individuals^6–8^. ET is usually diagnosed between the fifth and sixth decade, and has a longer life expectancy and a lower leukemic transformation rate as compared to other MPN^1^. However, up to 50% of ET patients experience a thrombotic event, including myocardial infarction, ischemic stroke, transient ischemic attack, or venous thromboembolism^1^, with an estimated incidence of 1.3–6.6% per year in spite of cytoreductive agents and/or antiplatelet drugs^9^. Thrombosis-related mortality in ET approximates 0.5% per year^9^, which ranks higher than the general population^10^. Accordingly, an optimal use of antiplatelet agents seems of outmost clinical relevance.

Several groups have reported increased in vivo platelet activation in ET^11–13^. In particular, we have previously described persistently enhanced urinary excretion of 11-dehydro-thromboxane (TX)B_2_ (TXM) in ET patients^11,12,14^. TXM is the major enzymatic metabolite of TXA_2_ in humans and is largely of platelet origin^15^, therefore its urinary excretion represents a widely used biomarker of platelet activation^9^, which is consistently increased in different clinical settings at high cardiovascular (CV) risk, and predicts CV events in aspirin-treated high-risk patients^16^. Thus, data in ET suggest a pathogenetic link between persistently enhanced platelet activation and thrombotic complications, requiring an effective antiplatelet therapy. Low-dose aspirin (75–100 mg once daily [od]^17^) is currently recommended for both secondary and primary CV prevention in the majority of ET patients^1,9^, with the exception of young patients without traditional CV risk factors, defined at “low risk”, in whom aspirin in primary prophylaxis remains controversial^18^ and possibly dependent on the mutation profile^19^.

The recommendation of using low-dose aspirin in ET patients is mainly based on retrospective, observational analyses^3,9^ and on the extrapolation from an aspirin trial for CV prevention in polycythemia vera^20^. However, controlled trials formally assessing the efficacy and safety of low-dose aspirin in ET are lacking. Thus, the recommendation of the same aspirin dose range (75–100 mg) and dosing regimen (od) for ET patients as for non-ET patients implies assuming similar antiplatelet pharmacodynamics.

The unique pharmacodynamics of low-dose aspirin relies on the irreversible acetylation of platelet cyclooxygenase (COX)-1 and the resulting long-lasting inhibition of TXA_2_ biosynthesis^21^. In spite of aspirin short half-life (20 min in the human circulation), blockade of platelet COX-1 activity lasts for the entire platelet life span due to the limited platelet capacity for new COX-1 synthesis, thus allowing od dosing^21^. Moreover, aspirin acetylates a variable fraction of COX isozymes in the bone marrow megakaryocytes and pro-platelets, as suggested by a 24–48 h delay between aspirin withdrawal and reappearance of COX-1-dependent TXA_2_ biosynthesis in peripheral platelets^22^. Thus, under normal thrombopoiesis, a 24-h dosing interval of a short-lived drug is ensured by a unique combination of irreversible inactivation of a slowly renewable drug target (platelet COX-1) and an effect on platelet progenitors, leading to a new platelet progeny with a largely non-functioning enzyme throughout the 24-h dosing interval^21^. Therefore, at steady state, low-dose aspirin inhibits platelet COX-1 activity by >97% in healthy subjects^22^, as assessed by a surrogate biomarker of efficacy, i.e., the measurement of ex vivo TXB_2_ production during whole-blood clotting^23^.

Low-dose aspirin reduces by ≈25% the rate of major CV events, in a variety of high-risk clinical settings^21,24^. However, at variance with non-ET patients, a standard od regimen of low-dose aspirin administration is inadequate to fully inhibit platelet TXA_2_ production in ≈80% of ET patients^12,14,25^. A faster renewal of the drug target, due to enhanced megakaryopoiesis, is both biologically and pharmacologically plausible in ET^14,26^. Accelerated platelet turnover is associated with a higher-than-normal fraction of newly released platelets with unacetylated COX-1 and/or COX-2^12^, which would account for incomplete inhibition as well as partial recovery of TXA_2_-dependent platelet function during the 24-h dosing interval^9^. Two independent studies have shown that the duration of the antiplatelet effect of low-dose aspirin is shortened in the majority of aspirin-treated ET patients, and incomplete suppression of platelet TXA_2_ production during the 24-h dosing interval can be largely rescued by a twice daily (bid) low-dose aspirin regimen^14,25^. However, approximately one-third of a small group (8 of 22) of ET patients treated with aspirin 100 mg bid still had persistently high serum TXB_2_ values^14^. Interestingly, an increased number of circulating immature platelets represents an independent determinant of poor antiplatelet drug response in non-ET disorders at high CV risk^22^^[,27,28^.

Thus, the abnormal megakaryopoiesis that characterizes ET appears to account for a shorter duration of the antiplatelet effect of low-dose aspirin due to a faster renewal of platelet COX-1, an abnormality that could be rescued by shortening the aspirin dosing interval, but not by increasing the od dose^14,25^. Based on the two small, proof-of-concept studies^14,25^, bid low-dose aspirin is currently considered in the most recent treatment algorithm for low- to high-risk ET patients^1^. However, the clinical efficacy and safety of a bid low-dose aspirin regimen in ET remains to be investigated. Moreover, it should be considered that multiple daily dosing of any drug is usually associated with a lower patient’s compliance^29^. Although a bid low-dose aspirin regimen has been successfully tested in stroke patients^30^, nevertheless this issue should be addressed when proposing multiple daily drug intake for further clinical evaluation.

The potential inhibitory effect of aspirin on vascular prostacyclin (PGI_2_) biosynthesis should also be considered. In fact, the COX-2 isozyme constitutively expressed in vascular endothelial cells largely accounts for PGI_2_ biosynthesis under physiological shear conditions^31^. In humans, PGI_2_ has vasodilator and platelet-inhibiting effects, counteracting pro-thrombotic signals, including platelet TXA_2_^31^. Od low-dose aspirin within the low-dose range has limited inhibitory effects on in vivo PGI_2_ biosynthesis, while it fully inhibits platelet TXA_2_ production, possibly because of differential rates of recovery of endothelial COX-2 vs. platelet COX-1 during the 24-h dosing interval^21,32,33^. It is unknown whether shortening the aspirin dosing interval may affect endothelial PGI_2_ production. A pilot study in 50 ET patients suggests that aspirin 100 mg bid does not significantly affect PGI_2_ biosynthesis^33^. However, the potential impact of a shorter dosing interval of low-dose aspirin administration on in vivo PGI_2_ biosynthesis should be investigated.

To address the open questions outlined above, we designed the Aspirin Regimens in Essential Thrombocythemia (ARES: EudraCT 2016-002885-30) trial as a phase II dose-finding study of aspirin in ET to select the optimal dosing regimen for an international phase III trial in ET. The ARES trial has been approved and funded by the Italian Medicines Agency (AIFA), study code FARM12Y8H.

## Study objectives

The ARES study has two primary objectives:To investigate whether aspirin regimens based on bid or three times daily (tid) administration of 100 mg result in a more complete suppression of platelet-derived TXA_2_ throughout the dosing interval, without significantly affecting in vivo PGI_2_ biosynthesis, as compared to the standard od regimen. Serum TXB_2_ will be measured as an index of platelet COX-1 activity, specifically reflecting the antiplatelet pharmacodynamics of aspirin (biochemical efficacy) (http://www.ema.europa.eu/docs/en_GB/document_library/Scientific_guideline/2009/09/WC500003340.pdf). A major urinary PGI_2_ metabolite, 2,3-dinor-6-keto-PGF_1alfa_ (PGIM) will be measured to assess the impact of different aspirin regimens on vascular COX-2 activity (biochemical safety)^32^. The comparison between aspirin 100 mg bid or tid vs. 100 mg od will test a superiority hypothesis in terms of serum TXB_2_ levels associated with each experimental vs. standard regimens. PGIM comparisons will assess the non-inferiority of any multiple daily dosing regimen vs. the standard od regimen. This objective will be addressed by a randomized, parallel-arm, double-blind, controlled study of 2-week aspirin treatment (part A) aimed at identifying the aspirin regimen to be further evaluated during long-term follow-up in the second part (part B) of the study.To evaluate the long-term persistence of superior biochemical efficacy of an optimized, multiple daily dosing regimen, as compared to the aspirin 100 mg od regimen. Biochemical efficacy will be assessed by repeated measurements of serum TXB_2_ (every 3 months over 20 months). A multiple daily dosing regimen will be tested for superiority vs. od dosing in terms of biochemical efficacy throughout the dosing interval, in an open-label, randomized study comparing aspirin 100 mg od vs. the optimal multiple daily dosing regimen identified in part A, with a follow-up of 20 months. This long-term follow-up will also provide an estimate of compliance with the experimental dosing regimen.

The secondary exploratory objectives will be:To assess the safety of the multiple daily aspirin regimen by recording: major bleeding and clinically relevant non-major bleeding events defined according to the Scientific and Standardization Committee of the International Society on Thrombosis and Haemostasis^34,35^, as well as any upper gastrointestinal non-bleeding adverse events, which may be considered attributable to aspirin (e.g., ulcer or perforation > grade 2).To record any thrombotic complication, as previously defined^3^. Briefly, major arterial thrombosis will include the following: acute coronary syndrome; any ischemic stroke (major and minor); and peripheral arterial thrombosis, including thrombotic digital ischemia and retinal arterial thrombosis. Major venous thrombosis will include thrombosis in the following districts: deep veins of the limb and/or abdomen; cerebral and splanchnic veins; retinal vein, as well as pulmonary embolism. Splanchnic venous thrombosis will include hepatic, portal, mesenteric, and splenic veins. Transient ischemic attack and superficial vein thrombosis of the limbs will be considered as minor thrombosis.To assess the tolerability of the experimental dosing regimen by recording the gastrointestinal symptoms by the severity of dyspepsia assessment questionnaire^36^.To evaluate the potential benefit of multiple doses of aspirin on the MPN-related symptom burden by a questionnaire aimed to capture all microvascular symptoms^37^, including the MPN Symptom Assessment and a pain numeric rating scale for erythromelalgia.To assess the stability over time of in vivo platelet activation, as assessed by urinary TXM excretion, in a subset of patients, in a non-invasive substudy.To assess whether the pre-fibrotic/early primary myelofibrosis (pre-PMF) phenotype now distinguished in the revised 2016 WHO classification^38^ has a higher incidence in the patients who will develop major or clinically relevant non-major bleeding during follow-up.

These secondary assessments will be performed in part B of the study, over 20-month treatment.

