### Part B

The experimental aspirin regimen associated with a significantly lower serum TXB_2_ level and non-inferior urinary PGIM excretion rate (i.e., ≤30% reduction) as compared to aspirin 100 mg od, will be selected for part B, and patients will be randomized in an open-label fashion to the standard vs. the optimized multiple dosing regimen for 20 months. The primary end point of part B will assess the long-term persistence of the superior biochemical efficacy of the optimized vs. standard aspirin regimen, in at least 6 out of 10 determinations of serum TXB_2_ that will be performed over 20 months. Secondary end points of part B will explore the following: (i) the safety of the experimental aspirin regimen, as reflected by any major bleeding and gastrointestinal symptoms considered attributable to aspirin; (ii) effectiveness in reducing MPN-specific symptom burden and pain attributable to microcirculatory disturbances; and (iii) stability over 20 months of the degree of platelet activation in vivo, as assessed by urinary TXM. The stability of TXM will be assessed in a subgroup of 150 patients.

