## Study end points and statistical analysis

The co-primary end points of part A are as follows: (1) platelet TXA_2_ production ex vivo, as reflected by serum TXB_2_, measured in samples collected in the morning, before the next aspirin intake; and (2) vascular PGI_2_ biosynthesis in vivo, as reflected by urinary PGIM excretion in a urine sample collected in the morning before the next aspirin intake. Urinary TXM excretion represents a secondary end point. These biomarkers will be measured at randomization and at 14 ± 2 days thereafter.

The primary end point of part B is represented by serum TXB_2_ measured 10 times in samples collected in the morning, before the next aspirin intake. The secondary end points are related to exploratory assessment of safety and tolerability of the experimental aspirin dosing regimen, and stability over time of in vivo platelet activation, as detailed above.

Based on previous findings^12,14^, we expect the mean ± standard deviation (SD) serum TXB_2_ in ET patients on aspirin 100 mg od and 100 mg bid to be 22 ± 33 and 5.0 ± 6.0 ng/ml, respectively. We plan to test with *α*-error of 0.05 and a *β*-error of 0.2 (power 80%) the following hypotheses:100 mg bid is superior to 100 mg od, with a ≥50% reduction in serum TXB_2_ (required sample size 70 patients/arm)100 mg tid is superior to 100 mg bid, with a ≥50% reduction in serum TXB_2_ (required sample size 70 patients/arm)

Anticipating a 30% dropout over the entire study duration, we plan to enroll 100 patients/arm to ensure adequate statistical power. For urinary PGIM, we expect the mean ± SD PGIM excretion rate in ET patients on aspirin 100 mg od to be 195 ± 119 pg/mg creatinine^33^. Using the above sample size (*n* = 70 patients/arm), the study has 80% power to test the hypothesis that any experimental treatment may reduce urinary PGIM to <140 pg/mg creatinine, i.e., by >30%. This threshold of PGIM inhibition vs. the standard dosing regimen can be considered reasonably safe based on the following considerations: urinary PGIM excretion is minimally affected by low-dose aspirin in healthy subjects^32,33^; in ET subjects, aspirin 100 mg bid did not significantly modify PGIM as compared to 100 mg od^33^; and this threshold corresponds to the intra-subject coefficient of variation on repeated measurements of PGIM excretion over time^39^.

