The same 300 ET patients will be randomized in part B of the study that will test the long-term persistence of superior biochemical efficacy of the optimized vs. standard dosing regimen. In all, 112 patients/arm will be needed to assess with an *α*-error of 0.05 and 80% power, a reduction of at least 50% in serum TXB_2_ with the optimized regimen (100 mg bid or tid) vs. the standard aspirin regimen (100 mg od), in at least 6 out of 10 determinations performed over 20 months.

Differences in mean serum TXB_2_ values will be evaluated by one-way analysis of variance, using Scheffe multiple-comparison test to allow comparisons of the three different treatments in part A. Analysis of covariance using multiple regression with dummies for the different treatments will be used if, at single univariate analysis, major differences (*p* < 0.05) in the distribution of gender, age, platelet count, JAK2 mutational status, spleen size, aspartate aminotransferase, alanine aminotransferase, or creatinine, and type of cytoreductive drug (if any) will be present between the three treatment subgroups. Both intention-to-treat and per-protocol analyses will be carried out.

It can be reasonably anticipated that a portion of the ET patients recruited in this trial according to the 2008 WHO diagnostic criteria^4^ might fall into the category of the pre-PMF according to the revised 2016 WHO criteria^38^. In a large international study of 1104 ET patients, diagnosis was revised to pre-PMF in 16%;^40^ these patients have been reported having an increased tendency toward bleeding^41^. Therefore, we will perform a pre-specified secondary analysis in the group of patients who will develop major and/or non-major clinically relevant bleeding in comparison with the patients with an uneventful course. All the bone marrow biopsies of the recruited patients will be revised by an ad hoc committee formed by the pathologist of the Coordinating Center and the pathologist of the Center where the patient had been recruited in order to assess whether patients had a true-ET or a pre-PMF according to the revised WHO classification;^38^ both the pathologists involved in the bone marrow revision will be blinded to the clinical characteristics of the patients. If the pathologists will provide different opinions, we will consult with a qualified third pathologist. The incidence of pre-PMF in patients with bleeding events will be compared to that found in non-bleeders.

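### Part B: serum TXB2 sampling every 3 months over 20 months gives 6 to 8 determinations, but the primary end point is defined on 10

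*Protocol article*

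**What the plan says.** The protocol article describes part B serum TXB2 sampling in four places.

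- **Study objectives, second primary objective:** "repeated measurements of serum TXB_2_ (every 3 months over 20 months", in a randomised open-label comparison "with a follow-up of 20 months".
- **Part B:** the primary end point is persistence of superior biochemical efficacy "in at least 6 out of 10 determinations of serum TXB_2_ that will be performed over 20 months".
- **Study end points and statistical analysis, end-point paragraph:** "The primary end point of part B is represented by serum TXB_2_ measured 10 times".
- **Study end points and statistical analysis, part B sample size:** "112 patients/arm will be needed to assess with an *α*-error of 0.05 and 80% power". The effect to be shown is TXB2 lower by half or more than under the once-daily regimen, and the same rule is attached to it: "in at least 6 out of 10 determinations performed over 20 months".

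The first place gives an interval and the other three give a count, all for the same 20 months. No text describes additional or unevenly spaced part B samples.

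**The concern.** The part B primary end point is a threshold count: the effect must be present at six or more of ten determinations. The denominator is therefore part of the definition. If the stated interval cannot produce that denominator, the end point cannot be evaluated as written under the stated schedule.

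Two outcomes would follow from sampling every 3 months. Either the threshold of six stays and is applied to fewer determinations, which makes the criterion harder to meet, or someone chooses a new denominator or threshold. Part B is open-label, so a choice made once data are accruing would be hard to defend as independent of the results.

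**Working it through.** **Inputs.** Interval 3 months and follow-up 20 months (Study objectives). Ten determinations, threshold six (Part B; Study end points and statistical analysis). Od mean ± SD 22 ± 33 ng/ml, reduction of at least 50%, α 0.05 with sidedness not stated, power 80%, 112 per arm (Study end points and statistical analysis).

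**Step 1. The count of ten.** 20 / 10 = 2, so ten post-baseline samples fit months 2, 4, …, 20 exactly. If the baseline is one of the ten, the spacing is 20 / 9 ≈ 2.2 months.

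**Step 2. The 3-month interval.** 20 / 3 = 6.67, so six whole intervals fit.

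| Samples counted | Number |
|---|---|
| Months 3, 6, 9, 12, 15, 18 | 6 |
| Plus baseline or month 20 | 7 |
| Plus baseline and month 20 | 8 |
| Stated | 10 |

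The shortfall is 2 to 4 of 10, or 20% to 40%. Ten determinations at 3-month spacing would take 9 × 3 = 27 months with the baseline counted, or 10 × 3 = 30 months without it.

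**Step 3. Could the part A samples fill the gap?** Part A has two samples, at randomisation and at 14 ± 2 days, and 8 + 2 = 10. But the article places all ten within the 20 months of part B. Part A is a separate randomisation, after which patients return to open-label standard aspirin. This reading fails.

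**Step 4. Does the sample size depend on the count?** For a single comparison of means, 22 against 11 ng/ml with SD 33:

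n per arm = 2 × 33² × (z_α + z_β)² / 11² = 18 × (z_α + z_β)²

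- One-sided 0.05: 18 × (1.645 + 0.842)² ≈ 111.3, rounded up to 112. This is the stated figure.
- Two-sided 0.05: 18 × (1.960 + 0.842)² ≈ 141.3, rounded up to 142.

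The stated 112 is reproduced as a single-time-point calculation. The number of determinations does not enter it.

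**Step 5. How much stricter is the rule with fewer determinations?** As an illustration, suppose independent determinations that each succeed with probability 0.7 (an assumption). The binomial chance of at least six successes is 0.85 with 10 determinations, 0.55 with 8, 0.33 with 7 and 0.12 with 6.

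A more realistic check simulates 112 per arm with lognormal TXB2. The coefficient of variation is 33 / 22 = 1.5, so the log-scale SD is √ln(1 + 1.5²) = 1.086. The true ratio is 0.5 and within-patient correlation runs from 0.3 to 0.9 (assumed).

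| How each visit is judged | 6 of 10 | 6 of 6 |
|---|---|---|
| Two-sided test, raw scale | 95–99% | 72–85% |
| One-sided 0.05, raw scale | above the two-sided figures | 83–92% |
| Two-sided test, log scale | about 100% | 98–99% |
| Observed reduction of 50% or more | 42–48% | 6–31% |

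With the raw two-sided test, 6 of 7 is met at least about 90% of the time and 6 of 8 at least about 93%. If the article's expected bid values (5.0 ± 6.0 ng/ml) replace the 0.5 ratio, 6 of 6 is met in more than 99% of runs on the raw two-sided test and in about 100% on the observed-reduction reading.

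**The case against.** **A slip in one parenthesis.** Ten appears three times, including in the end-point definition and the sample-size statement, and fits a 2-month interval exactly. The 3-month figure appears once, in the objectives. This argument stands as to which figure is the likelier error. It does not remove the conflict, and the article does not settle it.

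**Centres do not work from a journal article.** They would follow the full protocol, which is not shown; the trial-design figure is not shown either. This also stands. A reader might infer that centres will collect too few samples, but the documents do not show that. Nor is this mere condensation: the article prints both figures, and a schedule elsewhere could show which was meant without making them agree.

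**The power loss is a worst case.** A reader might infer from the 6-of-6 results that part B would be badly underpowered. The documents do not support that. They do not say that the threshold would stay at six with a smaller denominator, and 7 or 8 determinations are possible. The marked losses need a raw-scale test or a true effect placed exactly at the 50% threshold. In that last case each visit is close to a coin toss, and the rule already fails more often than not with ten determinations. A log-scale test or the article's own bid values make the loss negligible.

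**The sample size is unaffected.** Correct. It would be wrong to infer that 112 per arm is invalidated by this inconsistency.

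**Conclusion.** The inconsistency is real and follows from arithmetic alone. The stated interval yields 6 to 8 part B determinations and the primary end point needs 10; no reading of the text gives both. It should be corrected before part B starts, because interval and count together define a primary end point with a threshold rule.

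The consequence is conditional. Sampling every 3 months with the threshold kept at six would make the criterion 6 of 6, 7 or 8, stricter than stated. The loss of power then ranges from negligible to substantial, depending on the scale and sidedness of the test, the true effect and the within-patient correlation; the article does not fix these for the visit-level rule. No single power figure should be attached to this point.

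**What to change.** Reconcile Study objectives, Part B, and Study end points and statistical analysis before part B starts.

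- **Simplest route:** if ten determinations are intended, change the interval in the second primary objective to every 2 months. This is a one-line correction and adds no samples beyond the ten already stated. Say whether the baseline sample is one of the ten; if it is, the spacing is about 2.2 months.
- **If 3-monthly sampling is intended:** state the number of determinations it yields (6, 7 or 8, depending on baseline and month 20) and restate the success rule for that number in Part B, in the end-point paragraph and in the sample-size statement. This is a substantive amendment of the primary end point. It must be made prospectively, and the power under the new rule should be shown.

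If the full protocol already carries an unambiguous visit schedule, aligning the article with it is enough.
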